## Abstract

**Background:**

Eliminating hepatitis C is hampered by the costs of direct-acting antiviral treatment and the need to treat hard-to-reach populations. Access could be widened by shortening or simplifying treatment, but limited research means it is unclear which approaches could achieve sufficiently high cure rates to be acceptable. We present the statistical aspects of a multi-arm trial designed to test multiple strategies simultaneously and a monitoring mechanism to detect and stop individual randomly assigned groups with unacceptably low cure rates quickly.

**Methods:**

The VIETNARMS trial will factorially randomly assign patients to two drug regimens, three treatment-shortening strategies or control, and adjunctive ribavirin or no adjunctive ribavirin with shortening strategies (14 randomly assigned groups). We will use Bayesian monitoring at interim analyses to detect and stop recruitment into unsuccessful strategies, defined by more than 0.95 posterior probability that the true cure rate is less than 90% for the individual randomly assigned group (non-comparative). Final comparisons will be non-inferiority for regimens (margin 5%) and strategies (margin 10%) and superiority for adjunctive ribavirin. Here, we tested the operating characteristics of the stopping guideline for individual randomly assigned groups, planned interim analysis timings and explored power at the final analysis.

**Results:**

A beta (4.5, 0.5) prior for the true cure rate produces less than 0.05 probability of incorrectly stopping an individual randomly assigned group with a true cure rate of more than 90%. Groups with very low cure rates (<60%) are very likely (>0.9 probability) to stop after about 25% of patients are recruited. Groups with moderately low cure rates (80%) are likely to stop (0.7 probability) before overall recruitment finishes. Interim analyses 7, 10, 13 and 18 months after recruitment commences provide good probabilities of stopping inferior individual randomly assigned groups. For an overall true cure rate of 95%, power is more than 90% to confirm non-inferiority in the regimen and strategy comparisons, regardless of the control cure rate, and to detect a 5% absolute difference in the ribavirin comparison.

**Conclusions:**

The operating characteristics of the stopping guideline are appropriate, and interim analyses can be timed to detect individual randomly assigned groups that are highly likely to have suboptimal performance at various stages. Therefore, our design is suitable for evaluating treatment-shortening or -simplifying strategies.

**Trial registration:**

ISRCTN registry: ISRCTN61522291. Registered on 4 October 2019.

## Background

Oral direct-acting antivirals (DAAs) have transformed the treatment of hepatitis C virus (HCV). Compared with historical injectable interferon-based treatment of 6–12 months, they are more effective and better tolerated and offer shorter durations of therapy (8–12 weeks) [1]. However, access to treatment is still limited by costs, particularly in low-income countries where the patient pays at least in part [2]. Furthermore, achieving the World Health Organization (WHO) target for elimination of viral hepatitis as a public health threat by 2030 [3] will require curing hard-to-reach populations, including the homeless, drug users and prisoners who still find adherence challenging. Strategies designed to reduce drug exposure while still achieving HCV cure could further widen treatment access, but to date there has been limited research into shortening and simplifying HCV treatment with DAAs.

Previous very small studies assessing shortened DAA treatment have found higher cure rates when treatment length is guided by early response to treatment [4–6] or when adding adjunctive therapies, such as pegylated interferon (PEG-IFN) [7], to DAAs. Outside of HCV treatment, drug-sparing strategies that allow intermittent dosing are widely used in the treatment of tuberculosis [8], allowing patients who may not comply with daily treatment to access supervised treatment. Although these approaches may also be successful in HCV, no studies are currently assessing such a strategy with DAAs. There has also been little research into the use of DAAs in genotype 6, a strain that is most prevalent in Vietnam and surrounding countries (~50%) but uncommon elsewhere (<5%) [9]. Several small studies have shown very high cure rates with DAAs in this genotype [10–13], as in other genotypes, but these have been mostly limited in regimen and to standard-length courses. Finally, three pan-genotypic regimens (sofosbuvir/velpatasvir, sofosbuvir/daclatasvir and pibrentasvir/glecaprevir) are recommended by the most recent WHO guidelines [14], but to date there has been no direct randomised comparison of these regimens in any genotype.

As there are very few data to inform optimal ways to shorten HCV treatment, especially in genotype 6, it is possible that any proposed shortening strategy will fail. Therefore, trial designs that include many different options whilst allowing for the early stopping of unsuccessful treatments in order to focus on more successful treatments are essential, both for trial efficiency and to protect patients. Two trial designs that incorporate both of these aspects are factorial trials and multi-arm multi-stage (MAMS) trials. Both designs allow for greater efficiency in trials by reducing the number of patients required and shortening the time needed to test multiple interventions compared with sequential trials of individual interventions [15, 16]. Where an interaction between interventions being tested is anticipated, MAMS trials are preferred as this increases power to detect them [17]. However, the timing and maximum number of interim analyses within MAMS trials generally have to be pre-specified [18] or otherwise controlled with an alpha-spending function, which can be computationally difficult, particularly as the complexity of the design increases [19]. Therefore, MAMS designs may be less suitable for interventions where the effect on outcomes is unknown and the interim analysis schedule may have to be altered, at least where *a priori* interactions are not expected.

Data monitoring and stopping guidelines are most commonly framed within a frequentist framework with guidelines based on *P* values or conditional power. In the planning of interim analyses, it is generally accepted that care must be taken to control type I error, which can limit the ability to change the monitoring schedule to adapt to accumulating data, which may lead to delays in stopping unsuccessful treatments (e.g., if strict guidelines such as Haybittle–Peto (*P* <0.001) are used). Although strict error control may not always be necessary in a trial using frequentist methods [20], a more flexible approach to monitoring can be easier to implement and justify by using a Bayesian approach, which allows for stopping guidelines that are based on directly interpretable probabilities, particularly in complex multi-arm trials [21–24]. Incorporating Bayesian monitoring within a multi-arm factorial trial can allow for a flexible monitoring schedule to test multiple strategies and detect inferior ones quickly. Previous designs have looked at multi-arm trials [25, 26] but have not examined the impact of factorial randomisation.

Here, we present the statistical aspects of the design of a multi-arm factorial trial (to be conducted in Vietnam) that aims to find efficacious drug-sparing treatment strategies that will allow access to HCV treatment to be widened, and our particular focus is on increasing evidence on treatment of genotype 6.

## Methods

### Trial design

VIETNARMS is a parallel-group open-label factorial trial (ISRCTN61522291); 1092 patients will be factorially randomly assigned 1:1 to two different WHO-recommended dual DAA regimens (sofosbuvir/velpatasvir versus sofosbuvir/daclatasvir), 1:2:2:2 to the standard licensed 12-week treatment versus 4-week treatment with PEG-IFN + DAA versus 4- to 12-week response-guided therapy (RGT) versus 12-week treatment using an induction/maintenance approach, and (if not randomly assigned to standard 12-week treatment) 1:1 to adjunctive ribavirin versus no ribavirin for the duration of their DAA treatment (Fig. 1). Randomisation will be stratified by genotype 6 versus all other genotypes. Patients randomly assigned to the PEG-IFN strategy will receive DAAs for 4 weeks with weekly PEG-IFN for 4 weeks starting at day 7. Treatment length for those randomly assigned to RGT will be determined by HCV viral load (VL) at day 7 and based on predicted viral kinetics [27]: those with VL of less than the lower limit of quantification (LLOQ) will receive 4 weeks of treatment, those with VL LLOQ-250 IU/mL will receive 8 weeks and all others will receive 12 weeks. Patients randomly assigned to induction/maintenance will receive 12 weeks of treatment: 2 weeks of daily treatment (induction phase) followed by 10 weeks of 5-day treatment per week, taking weekends off from the first weekend following their full 2-week treatment. Each strategy reduces DAA exposure and has other benefits, such as compatibility with directly observed therapy programmes (as used for tuberculosis) but with other additional costs (Table 1). Within the trial, any patient not achieving cure with their first-line treatment will receive 12 weeks of retreatment with the alternate drug regimen to the one they were originally randomly assigned plus ribavirin.

**Fig. 1 Fig1:**
[figure not shown]
Trial schema. *Abbreviations*: *PEG-IFN* pegylated interferon, *RBV* ribavirin, *RGT* response-guided therapy, *SOF/DCV* sofosbuvir/daclatasvir, *SOF/VEL* sofosbuvir/velpatasvir, *VL* viral load.

**Table 1 Tab1:** Components of each shortening strategy and cost differences compared with standard 12-week treatment

Shortening strategy	Resource use of providing treatment				Difference in cost compared with standard 12-week treatment
	Mean weeks of DAA	Number of PEG-IFN injections	Number of visits required	Number of VL tests	
Standard 12-week treatment	12	0	3^a^	1^a^	–
PEG-IFN + DAA (4 weeks’ treatment, weekly PEG-IFN)	4	4	6	1	-8x(weekly drug cost) + 4x(interferon cost) + 3x(visit cost)
Response-guided therapy (4, 8, or 12 weeks’ treatment)	9.6^b^	0	4	2	−3.4x(weekly drug cost) + 1x(visit cost) +1x(VL cost)
Induction/maintenance (7 days/week for 2 weeks, then 5 days/week)	9.14	0	4^c^	1	−3.86x(weekly drug cost) + 1x(visit cost)

*Abbreviations*: *DAA* direct-acting antiviral, *PEG-IFN* pegylated-interferon, *VL* viral load.

^a^ Assuming minimum visits at treatment initiation, end of treatment, end of treatment plus 12 weeks (where VL is done once to assess cure)

^b^ Assuming 1:3:1 receiving 4:8:12 weeks of treatment. One extra visit and VL at day 7 to assess initial VL response

^c^ Assuming one extra visit at week 2 when move from induction to maintenance phase

### Primary endpoint

The primary endpoint is sustained virologic response (SVR12), namely virological cure on first-line therapy defined as plasma HCV VL of less than LLOQ 12 weeks after the end of first-line treatment (EOT + 12) without prior failure. Failure is defined as either two consecutive HCV VLs of more than LLOQ after two consecutive HCV VLs of less than LLOQ with the latter confirmatory VL of more than 2000 IU/mL or two consecutive HCV VLs of more than 1 log_10_ increase above HCV nadir on treatment and of more than 2000 IU/mL (either definition being met whilst on treatment or after finishing treatment during follow-up). The primary outcome is binary, and all observed endpoints are either SVR12 or treatment failure.

These failure criteria identify patients who, were they not to receive retreatment before EOT + 12 weeks, would definitively have HCV VL greater than LLOQ at 12 weeks post-EOT and hence would be considered failures in the primary endpoint. However, for ethical reasons, within the trial such patients will be offered retreatment as soon as they are definitively identified as having failed first-line treatment. Failure is defined using a higher threshold than the LLOQ because patients have been observed to achieve cure despite having low-level viraemia at EOT or shortly after and so they do not need retreatment to achieve cure on first-line treatment. In practice, any participant with low-level viraemia of less than 2000 IU/mL either cures or VL rises above this level. This will be carefully reviewed by the independent data monitoring committee (DMC). This is the same definition as used in the UK STOP-HCV-1 trial (ISRCTN37915093) and SEARCH-1 trial in Vietnam (ISRCTN17100273), where the DMC has similarly reviewed individual patient VL trajectories.

### Monitoring

For the strategies to be viable outside the trial, first-line cure rates need to be high (>90%). The design of the trial therefore allows for failing groups to be stopped early at any time and subsequent patients to be randomly assigned to more successful groups. Individual performance of groups receiving shortening strategies will be monitored during recruitment by an independent DMC that will make decisions on whether a group should be stopped. Groups receiving standard 12-week treatment will not be monitored as this is the licensed duration with cure rates of more than 90% [28, 29]. Interim analyses will not be comparative as the aim of monitoring is not to find the best strategy but to find any strategy that meets a minimum acceptable cure rate that may also be non-inferior to standard treatment as different strategies may benefit different patient populations.

Analyses of cure rates will follow the Bayesian paradigm to allow the probability of the true cure rate being below different thresholds to be calculated: recruitment into a group will stop if there is a greater than 0.95 posterior probability of the true cure rate being less than 90% (Pr(true cure rate <0.9|x) >0.95, where x is the data currently observed). The primary monitoring is combined across genotypes; if the combined group reaches the stopping guideline, each genotype stratum will be tested separately and the DMC will have the discretion to stop only those strata reaching the stopping criteria. Differences in stopping groups across strata are likely to occur only when there are extreme differences in the cure rates between the strata, which is not expected, and so the operating characteristics of the trial are based on stopping combined strata only. If neither stratum reaches the stopping criteria despite the combined strata doing so, it will be at the discretion of the DMC whether to stop recruitment into the stratum or group.

At interim analyses, there is greater uncertainty about the performance of the shortening strategies. Therefore, when the prior was determined, it was assumed that one strategy would fail completely such that all four groups receiving that strategy, of a total of 12 tested, would meet the stopping guideline. As each individual outcome is assumed to be Bernoulli-distributed and therefore distribution of all outcomes is binomial, a beta prior was chosen as this is the conjugate prior for the binomial distribution. The mean of the prior was fixed at 0.9, and the effective sample size of the prior was varied until a distribution was found such that there was a roughly 0.33 probability of a cure rate of less than 90%; roughly 0.33 probability was chosen as 4 out of 12 randomly assigned groups are expected to fail and therefore have a true cure rate of less than 90%. The prior chosen was beta (4.5, 0.5) with mean 0.9, variance 0.015 and a 0.34 probability of a cure rate of less than 90%. The relatively low precision of the prior will allow greater influence of the data in the posterior distribution. If the stopping guideline is met, sensitivity analyses using priors informed by observed cure rates in other randomly assigned groups or strata will be performed and will be provided to the DMC to help inform their decision to stop a group.

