Total recruited	205	361	517	777
Total at EOT + 12 weeks	44	144	286	533
At EOT + 12 weeks in each:				
PEG-IFN group	5	14	24	42
RGT group	3	11	21	39
Induction/maintenance group	2	8	17	35
Average probability genuinely inferior group will be stopped^a^				
PEG-IFN groups	0.124	0.297	0.537	0.710
RGT groups	0.021	0.313	0.440	0.665
Induction/maintenance groups	0.070	0.150	0.431	0.593

*Abbreviations*: *EOT + 12* 12 weeks after the end of treatment, *PEG-IFN* pegylated-interferon, *RGT* response-guided therapy

^a^ Assuming true cure rate uniformly distributed over 60–90%

As this is only projected recruitment, sensitivity analyses were performed to examine the effect of faster or slower recruitment (Supplementary Table 3, Additional file 1). These indicate that changes to the recruitment schedule alter only the timing of the analyses; the number of patients in each analysis differs by less than the estimated number recruited in 1 month. Therefore, if there are significant delays in recruitment, interim analyses will be timed such that they include a similar number of patients at EOT + 12 to that in the expected schedule. Sensitivity analyses also explored changing the lower bound of the distribution over which cure rates of genuinely inferior groups are assumed to be distributed to below 60% (Supplementary Table 4, Additional file 1) but this had minimal effect on the timing of initial interim analyses. There were greater differences in the timings of the last analyses, but the timing of this analysis is the most flexible and can be determined on the basis of observed rather than assumed true cure rates.

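### The stopping rule does not say that failures confirmed before EOT + 12 are held back, although its published operating characteristics assume a cohort of patients at EOT + 12

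*Protocol article*

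**What the plan says.** **The rule (Methods, Monitoring).** The text reads "recruitment into a group will stop if there is a greater than 0.95 posterior probability of the true cure rate being less than 90" per cent, with x described only by "where x is the data currently observed". The Table 3 footnote and the Alternative designs section describe x in the same way. The prior is a beta distribution: "The prior chosen was beta (4.5, 0.5) with mean 0.9, variance 0.015".

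**The endpoint (Methods, Primary endpoint).** Cure is "plasma HCV VL of less than LLOQ 12 weeks after the end of first-line treatment (EOT + 12) without prior failure", so it cannot be recorded sooner. Failure needs confirmed viral loads, "either definition being met whilst on treatment or after finishing treatment during follow-up". A failing patient is not left until EOT + 12: "such patients will be offered retreatment as soon as they are definitively identified as having failed first-line treatment". The same section says that "all observed endpoints are either SVR12 or treatment failure".

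**The operating characteristics (Results and Discussion).** Table 3 computes stopping probabilities from the binomial distribution for each number of analysed patients and concludes that, at a true cure rate of 90%, incorrect stopping is always below 0.05. The text on the overall probability of stopping keeps that limit for cure rates above 90%. Table 4 counts patients under the label "At EOT + 12 weeks in each", followed by the strategy groups. The section on timing sizes the looks, and re-times them if recruitment is slow, by patients at EOT + 12.

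**The concern.** The two outcomes do not become known at the same time. A cure takes 16 weeks from the start of treatment in the PEG-IFN groups (4 + 12) and 24 weeks in the induction/maintenance groups (12 + 12). A failure can be known earlier. Recruitment is still open at every planned look, so each look has patients who have started treatment but not reached EOT + 12. Some may already be confirmed failures; none can be a confirmed cure.

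Taken literally, the observed data at a look are all patients past EOT + 12 plus the early failures among the rest. That set is enriched for failures and is not a binomial sample, so Table 3 does not describe it. The error would run in one direction, towards stopping groups that are at or just above the target. The article says that retaining groups above 90% matters more than stopping those slightly below it.

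**Working it through.** **1. Reproducing Table 3.** With n analysed patients and f failures, the posterior is Beta(4.5 + n − f, 0.5 + f). The threshold f*(n) is the smallest f for which the posterior probability of a cure rate below 0.9 exceeds 0.95. This gives 3 failures for n = 3–7, 4 for 8–13, 5 for 14–20, and so on to 13 for 72–78, matching all 12 rows. The binomial tail at 90% cure peaks at 0.048, as printed. Table 3 is right for the cohort it assumes.

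**2. An example by hand.** At month 7, Table 4 has 205 patients recruited. Each of the 14 groups takes 1/14, so about 14 per group, of whom 5 in a PEG-IFN group are at EOT + 12 and about 9 are pending. Suppose 1 failure among the 5 and 2 confirmed early failures among the 9.
- Literal x: 3 failures in 5 + 2 = 7. The posterior is Beta(8.5, 3.5), and Pr(cure < 0.9) = 0.957. The guideline is met.
- Cohort at EOT + 12 only: 1 failure in 5. Table 3 needs 3. Not met.
- The same 14 patients if the other 7 pending patients are cured: 3 failures in 14. The posterior is Beta(15.5, 3.5), and Pr(cure < 0.9) = 0.833. Table 3 needs 5. Not met.

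**3. Cumulative false stops over the four looks.** Inputs from Table 4 (patients at EOT + 12 per group at months 7, 10, 13 and 18): PEG-IFN 5, 14, 24, 42; RGT 3, 11, 21, 39; induction/maintenance 2, 8, 17, 35. The recruitment curve is in the Fig. 2 legend; months 0–4 are not given and were interpolated.

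With true cure rate p:
- Date-defined cohort: F ~ Bin(n, 1 − p); stop if F ≥ f*(n).
- Literal reading: F = Fc + Fe, with Fc ~ Bin(n, 1 − p) and Fe ~ Bin(m, (1 − p)q); stop if F ≥ f*(n + Fe).

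Here m is the number of pending patients within the assumed lead time of EOT + 12, and q is the share of their failures already confirmed. Neither the lead time nor q is in the article. Results by simulation at p = 0.90 and q = 1:

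| Failures confirmed | PEG-IFN | RGT | Induction/maintenance |
|---|---|---|---|
| Counted only at EOT + 12 | 4.7% | 5.2% | 4.4% |
| 4 weeks earlier | 8.0% | 9.0% | 7.0% |
| 8 weeks earlier | 13% | 14% | 12% |
| 12 weeks earlier | 19% | 19% | 17% |

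A separate simulation that followed individual patients along the recruitment curve gave 5.4–5.6% for the date-defined cohort, then 8–10%, 12–14% and 17–19%.

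**4. Sensitivity.**
- Fewer pending failures known: at 90% cure the ratio to the date-defined cohort is about 1.3, 1.8 and 2.3 for leads of 4, 8 and 12 weeks with q = 0.5, and about 1.15, 1.4 and 1.6 with q = 0.25.
- True cure 92.5%, q = 1: 1.3–1.5% becomes 2.4–2.9% (4 weeks), 4.5–5.1% (8 weeks) and 7.1–8.0% (12 weeks).
- True cure 95%: 0.2–0.4% becomes at most about 2.2% here, and no more than about 2.5% in any of the checks.

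**The case against.** The strongest reply is that the article already means a cohort at EOT + 12. The discussion of Table 3 speaks of failures among the first patients to reach that point; the timing section and Table 4 count only such patients; and the Limitations section explains look timing by the short PEG-IFN treatment, which fits a date-based cohort. On this view the wording quoted from Monitoring is notation: Alternative designs uses it to contrast interim data with complete data. The remark that endpoints are SVR12 or failure says only that the outcome is binary. A data-cut filter may also sit in the full protocol or a DMC charter.

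Much of this stands. A reader might infer that the plan will over-count failures at every look, or that false stops will double or triple. The documents do not support either. The first is a risk from wording, and the second depends on an assumed lead: the ratio at 90% cure runs from about 1.1 to about 4. Nor do they support saying that groups would be stopped automatically, since the DMC decides, receives sensitivity analyses with other priors, and reviews viral load data. The date-defined cohort is itself close to 5% cumulatively at exactly 90% cure, so only the excess over that is due to early failures.

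What does not stand is that nothing needs changing. The rule is defined in three places and none restricts x, while the endpoint section makes an early confirmed failure an observed endpoint. DMC review does not repair a posterior computed on the wrong set, and sensitivity priors built from observed cure rates in other groups would carry the same distortion.

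**Conclusion.** The point holds as a mismatch between the rule as worded and the cohort for which its properties were calculated. Tables 3 and 4 are sound for patients at EOT + 12, which is probably what is meant. If early confirmed failures were let into the posterior, the below-0.05 assurance would not hold at a true cure rate of 90%: about 5% over four looks would become roughly 7–10%, 12–14% or 17–19% for confirmation 4, 8 or 12 weeks before EOT + 12.

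Those figures assume that every failure among patients inside the lead window is already confirmed, and they use an interpolated early recruitment curve. With partial knowledge the rise is smaller. A reader might also infer that the assurance fails generally for groups above 90%. It does not: at 92.5% cure the limit is roughly reached at an 8-week lead and clearly exceeded only at 12 weeks, and at 95%, the overall rate assumed for power, false stops stay at or below about 2.5%. This should be fixed, but it is not a fundamental flaw.

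**What to change.** Add one sentence to Monitoring: at each interim analysis, x includes a patient, cured or failed, only if the scheduled EOT + 12 date has passed by the data cut. The date should be computed from the treatment start and assigned duration (known after day 7 for RGT), so that an early failure does not bring its own entry forward. The Table 3 footnote and Alternative designs can refer to that definition. Failures confirmed earlier should go to the DMC as a separate listing, outside the posterior calculation.

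The cost is that sentence and a date filter in the interim program; Table 3 needs no recalculation for this. The downside is small: early failures enter the formal rule some weeks later, so a genuinely poor group may meet the guideline slightly later, although the DMC still sees those failures as they occur.
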